### Study setting and randomization

The study will be conducted in 40-45 community health centers (CHCs) in Beijing, China, as the unit of randomization. The community health center contains 8-10 people with T2DM. A computer-generated list of random numbers will assign clusters (CHCs) in a 1:1 ratio to an intervention group and a control group. All subjects in each cluster will receive the same intervention (SDPC plus AI-HEALS) or control (SDPC). Blinding of the participants or researchers cannot be guaranteed considering the nature of the intervention. The proportion of sociodemographic characteristics (such as gender, age, and location) between two groups will be evaluated at baseline to verify that the data are balanced and comparable. Study designer will generate the allocation sequence, CHCs staff will enroll participants, and study designer will assign participants to interventions.

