### Effect size

Based on our previous study, assuming an alpha risk of 0.05, a beta risk of 0.10, an intraclass correlation (ICC) of 0.002, a mean level of HbA1c in patients with type 2 diabetes of 7.13%, and a standard deviation (SD) of 1.60%, at least 2 clusters, and 166 subjects (138 total before considering a dropout rate of 20%) in each cluster are expected to be recruited according to the sample size formula for unmatched studies [66] to detect a decrease in HbA1c to 6.50% after the intervention. As a result, a total of 664 patients in 4 communities are required to be recruited for this program.

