### Outcomes

Primary outcome: Change of HbA1c from baseline to 1, 3, 6, 12, and 18-month follow-up.

Secondary outcomes:1. Modifications of self-management behaviors: dietary, physical activity, blood glucose monitoring, and medication adherence.2. Social cognition and psychology: diabetes health literacy, self-efficacy, depression, anxiety and stress.3. Metabolic control: self-reported fasting plasma glucose or 2 h plasma glucose, dose of insulin and medicine, other indicators such as blood pressure, blood lipids, and BMI.4. Economic evaluation: A comparison of incremental cost-effectiveness ratios (ICERs) will be conducted between the AI-HEALS-based intervention and usual care of T2DM. Therefore, health-related quality of life (HRQoL), healthcare utilization, including medical consultations, use of healthcare (outpatient, hospitalized, and primary care services), medicine purchases, accident visits, and direct non-medical costs (diabetes-related transportation, lodging) will be collected.

Additionally, the rate of recruitment and drop-out, as well as the reasons for drop-out, will be gathered. To determine whether the data is homogeneous, demographic characteristics and study outcomes will be compared between people dropping out and participants resistant to the entire trial during data analysis.

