### Statistical analysis

Data from the quantitative study will be recorded in the designed questionnaire and double-parallelly entered into Epidata 3.1 (Version 15.0.5, Odense, Denmark). Variables analysis will be based on the premise of intention to treat. Continuous variables will be presented as mean ± SD (M(P_25_, P_75_), if they are abnormal distribution), and be compared using Student's t test or one-way ANOVA (or non-parametric tests if necessary). Data distribution will be identified by a Kolmogorov–Smirnov test. Categorical data reported as n(percentage of sample) will be compared using χ2 tests. With regard to the cross-sectional analysis, linear regression, logistic regression and structural equation model (SEM) will be conducted to explore the influence factors of behaviors pattern and mHealth usage pattern evaluated by the group-based trajectory model (GBTM). For longitudinal data, a generalized linear mixed model (GLMM) will be used to identify the effectiveness of the AI and mHealth-based intervention in behavioral changes and diabetic control. Set an alpha risk of 0.05 for two-sided tests. Data will be analysed using IBM SPSS Statistics version 24.0 (SPSS Inc., an IBM Company, Chicago, Illinois, USA), Stata (version 14.0, Stata Corporation, College Station, TX) and M*plus* (version 7.4, Muthén & Muthén, Los Angeles, CA, USA).

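### The primary outcome is change in HbA1c, and no baseline HbA1c term is stated for the mixed model; prespecifying one would gain precision at no cost in data

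*Protocol article*

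**What the plan says.** Under Outcomes, the primary outcome is "Change of HbA1c from baseline to 1, 3, 6, 12, and 18-month follow-up". Table 1 (Variables measurement) marks HbA1c at months 0, 3, 6, 12 and 18, so a baseline value will exist for analysis. (The absence of a month-1 mark is a separate matter.)

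The Statistical analysis section assigns effectiveness to one model: "For longitudinal data, a generalized linear mixed model (GLMM) will be used to identify the effectiveness of the AI and mHealth-based intervention". It lists no fixed effects, covariates or random effects. A separate, general sentence there covers t tests, ANOVA and non-parametric tests for continuous variables.

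On baseline comparability, Study setting and randomization says that sociodemographic proportions "between two groups will be evaluated at baseline to verify that the data are balanced and comparable". Its examples are gender, age and location; HbA1c is not among them. Health centres (CHCs) are allocated 1:1 from a random list, with no stratification or matching named.

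**The concern.** Baseline HbA1c can be expected to be among the strongest predictors of follow-up HbA1c, and the trial measures it in any case. Subtracting it fixes its coefficient at 1, whereas regression estimates the coefficient. Whenever r is below 1, subtraction over-corrects: it adds noise, and if the arms differ at baseline by chance it leaves part of the regression to the mean in the estimate. A mixed model with baseline as one of the outcomes and a free arm-by-time interaction does not avoid this. With complete data its interaction contrast equals the difference in mean change.

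The baseline check cannot help here. It does not name HbA1c, and comparing arms corrects nothing. At stake are some precision in the primary estimate and a small residual of chance imbalance. There is also a prespecification point. The Study management section leaves the choice of statistical methods to expert advice during data analysis, in a trial where blinding of researchers cannot be guaranteed. It is better to settle this covariate beforehand.

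**Working it through.** **Inputs from the article.** Effect size section: "assuming an alpha risk of 0.05, a beta risk of 0.10, an intraclass correlation (ICC) of 0.002"; mean HbA1c 7.13%; SD 1.60%; sized "to detect a decrease in HbA1c to 6.50% after the intervention", so the difference is 7.13 - 6.50 = 0.63. Statistical analysis: "Set an alpha risk of 0.05 for two-sided tests". Study setting and randomization: 40-45 CHCs of 8-10 patients. The baseline-to-follow-up correlation r is not given; 0.3 to 0.8 is my assumption.

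**Step 1. The plan's own figure.** Without clustering, n per arm = 2 × [1.60 × (1.960 + 1.282)/0.63]² = 135.5, or 136. The unmatched cluster formula with 2 clusters per arm, and with 0.002 entered as a between-cluster coefficient of variation, gives 136.9 per cluster, or 137 (stated: 138). Then 138 × 1.2 = 165.6, or 166, and 4 × 166 = 664. The stated size therefore reproduces closely. It rests on the SD of HbA1c levels, so it takes no credit for baseline HbA1c, either as a change score or as a covariate.

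**Step 2. Variances.** With equal SD s at baseline and follow-up and one follow-up visit:

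- change score: 2s²(1-r)
- baseline-adjusted: s²(1-r²)
- ratio, adjusted to change: (1+r)/2

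| r | ratio | reduction | n per arm, change | n per arm, adjusted |
|---|---|---|---|---|
| 0.3 | 0.65 | 35% | 190 | 124 |
| 0.4 | 0.70 | 30% | 163 | 114 |
| 0.5 | 0.75 | 25% | 136 | 102 |
| 0.6 | 0.80 | 20% | 109 | 87 |
| 0.7 | 0.85 | 15% | 82 | 70 |
| 0.8 | 0.90 | 10% | 55 | 49 |

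The n columns are for 90% power at two-sided 0.05, before clustering and dropout.

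**Step 3. Check by simulation.** With 21 CHCs per arm, 9 patients each and ICC 0.002, the standard errors for change and adjusted analyses were 0.192 and 0.156 at r = 0.3, 0.168 and 0.144 at r = 0.5, and 0.128 and 0.119 at r = 0.7. The squared ratios are about 0.66, 0.74 and 0.87, in line with 0.65, 0.75 and 0.85.

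**Step 4. Chance imbalance.** With the same layout there are 189 patients per arm and the design effect is 1 + 8 × 0.002 = 1.016. The standard error of the baseline difference is 1.60 × √(2 × 1.016/189) = 0.166, about 0.17. A change score leaves (1-r) times the imbalance. For a one-standard-error imbalance that is 0.5 × 0.166 = 0.083 at r = 0.5 and 0.3 × 0.166 = 0.050 at r = 0.7. Against 0.63 these are 13% and 8% of the target.

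**The case against.** The strongest reply is that nothing stated is wrong. The article names a class of model and no terms at all; by the same reading, arm, visit and CHC would also be missing. A covariate list commonly sits in the statistical analysis plan, which is not shown. If that plan has baseline HbA1c as a covariate, or a common baseline mean for the two arms, essentially nothing is lost. This stands, and it limits the point to a request to state the adjustment.

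Other parts of the reply also stand:

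- A reader might infer that the trial relies on the sociodemographic check in place of adjustment. The article does not present the check that way.
- A reader might take the t test to be the primary analysis. That sentence is general, and effectiveness is assigned to the mixed model.
- A reader might say that protection against imbalance is given up. Change from baseline does use baseline HbA1c and removes the direct difference; only about (1-r) of it remains. An imbalance as large as half the target (0.315, or 1.9 standard errors) has a probability of roughly 6%.
- Larger savings, of 1-r², would apply against a comparison of follow-up levels alone, which is not the stated outcome.
- No power shortfall follows. At r of 0.5 to 0.7 the change score needs 136 to 82 per arm, no more than the 136 behind the plan.

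What the reply does not remove is that the outcome is fixed as a change. Followed as written, this gives the less precise contrast at every r below 1.

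**Conclusion.** The point holds as a free improvement to the stated change-score outcome, and not as an error in the plan. The documents do not support saying that the trial has decided against baseline HbA1c. They support saying that the adjustment is unstated, while the outcome as defined leads by default to a less efficient estimate.

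The gain is a 15-25% lower variance for r of 0.7 to 0.5, and 10-35% over the wider range. It also removes a residual of about 0.05-0.08 HbA1c points for a typical chance imbalance. These figures assume equal SDs at baseline and follow-up, a single follow-up visit, the stated ICC of 0.002, and an r that the article does not supply. The imbalance figure also assumes about 21 CHCs of 9 patients per arm. The Effect size section instead describes 4 communities of 166, a conflict to be reconciled separately. The direction of the result does not depend on r or on which layout is right.

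**What to change.** State in the protocol or analysis plan, before any outcome data are seen, that the primary mixed model takes follow-up HbA1c as the response, with arm, visit and arm-by-visit effects and baseline HbA1c as a fixed covariate, alongside random effects for CHC and participant. An equally good choice is a longitudinal model that includes the baseline measurement and constrains its mean to be equal in the two arms. The result can still be reported as a difference in change, because the two differ only by a constant once baseline is adjusted for. Whether the baseline coefficient varies by visit can be left to the analysis plan.

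Reword the baseline comparison as a descriptive table that includes HbA1c, with no decision on adjustment hanging on it. The cost is one model term and a sentence or two of text; no new data are needed.

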### Study management

Prior to the study, the investigators will be trained and assessed comprehensively. Throughout the study, the study subjects will be registered and coded to minimize the occurrence of missing visits during the follow-up period. To maintain consistency between the intervention and control groups, survey time and questionnaire will be kept substantially identical. During data analysis, a double-entry checking procedure will be implemented to enhance the quality of data entry, and experts will be consulted to select appropriate statistical methods. If finding abnormal values, the original questionnaires will be checked and verified for accuracy to proceed to the analysis. Additionally, the qualitative data will be collated and proofread by two researchers to ensure reliability in the analysis of the qualitative findings.

The research leaders and primary investigators will supervise research implementers regularly to ensure the correct implementation of all research procedures and to guarantee the accuracy of the collected data. If investigators are failure to adhere to predefined survey and follow-up standards, research leaders will terminate the trial, revise the randomization scheme and recollect data after the modification is completed. In the event of fundamental or widespread design errors or inaccuracies in the research questionnaire during the survey process, the researchers will halt the trial to modify and redesign the questionnaire. After the necessary revisions were completed, the revised questionnaire will be then redistributed to participants.

The data monitoring committee (DMC) will be composed of at least two members from the Biomedical Ethics Committee of Peking University, who have no conflicts of interest with our study. The DMC will conduct regular monitoring and review of the study, and will report the findings to the Ethics Committee. This process will operate independently of the primary investigators. If the DMC identifies deviations from the approved research protocol or unauthorized changes to the study procedures during the research process, they have the authority to suspend or terminate the study. Furthermore, during the research, the project researchers are responsible for promptly reporting any serious adverse events (SAE) or adverse events (AE) to the Ethics Committee. If any participants experience AE or SAE, regardless of their relationship to the research intervention or whether the intervention has been implemented, the researchers must notify the investigators within 24 h of the event and terminate the trial. Additionally, in the event of serious program bugs or significant deficiencies in user interaction during the participant's engagement with AI, the researchers must interrupt the trial, redesign the study, and rectify the issues with the AI program.

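### The rule that answers investigators' survey or follow-up failures with a revised randomisation replaces the allocation after data exist, does not repair the fault, and is not required to be independent of results

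*Protocol article*

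**What the plan says.** All references are to the protocol article.

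- **Study management, trigger:** "If investigators are failure to adhere to predefined survey and follow-up standards".
- **Study management, consequence:** "research leaders will terminate the trial, revise the randomization scheme and recollect data after the modification is completed". The verb is mandatory, not permissive.
- **Study setting and randomization, allocation:** "A computer-generated list of random numbers will assign clusters (CHCs) in a 1:1 ratio to an intervention group and a control group".
- **Study setting and randomization, roles:** "Study designer will generate the allocation sequence, CHCs staff will enroll participants, and study designer will assign participants to interventions".
- **Study setting and randomization, blinding:** "Blinding of the participants or researchers cannot be guaranteed considering the nature of the intervention".
- **Statistical analysis:** "Variables analysis will be based on the premise of intention to treat", and "Set an alpha risk of 0.05 for two-sided tests".

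Study management also describes a data monitoring committee. It can suspend or stop the study when it finds departures from the approved protocol or changes that nobody authorised.

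**The concern.** Missed survey or follow-up standards are a conduct problem in a running trial. They say nothing about whether the centres were properly randomised, so redrawing the allocation does not address them. Because follow-up standards are part of the trigger, the rule can fire after centres have been allocated and data collected. The instruction to collect data again presupposes that some were collected before.

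Three things are then at stake:

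- The allocation analysed would no longer be the one first drawn, although intention to treat means analysis by the original allocation.
- Nothing in the rule requires the decision to be taken without regard to results, and the article does not guarantee that researchers are blinded.
- If the same centres take part again, some that have used AI-HEALS may become controls.

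The monitoring committee's powers, as described, do not close the gap. A redraw made under this rule is authorised by the protocol, so it is neither a departure from it nor an unauthorised change.

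**Working it through.** The plan attaches no figure to this rule. The sample size (4 × 166 = 664) plays no part in the point. The inputs taken from the article are the 1:1 allocation of centres, the 40-45 centres, and the two-sided alpha of 0.05, which gives 0.025 for a result favouring the intervention. Everything else below is an assumption and is marked as one.

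**1. Does a restart by itself inflate the error?** Assume that the restart is unrelated to results, that the new clusters are unexposed, and that only new data are analysed. In a simulation of 2,000,000 trials with no true effect and a restart in a random half, the favourable error was 0.025 and the two-sided error 0.050. There is no inflation.

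**2. What if the restart depends on results?** Assume that the leaders know the interim test statistic z and restart when it falls below a cut-off c, and that only the new data count after a restart. Then

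favourable error = P(restart) × 0.025 + P(no restart and the first attempt is significant in favour).

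When the decision is made on the complete first data set and c is at most 1.96, this is Φ(c) × 0.025 + 0.025:

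- c = 0: 0.5 × 0.025 + 0.025 = 0.0375
- c = 1: 0.841 × 0.025 + 0.025 = 0.046

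The simulation agrees, and also covers a decision at half the information:

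| Assumed trigger | Information at decision | Favourable error | Two-sided error |
|---|---|---|---|
| z < 0 | 50% | 0.037 | 0.050 |
| z < 0 | 100% | 0.037 | 0.050 |
| z < 1 | 50% | 0.041 | 0.063 |
| z < 1 | 100% | 0.046 | 0.067 |

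A more extreme trigger, restarting on anything short of z = 1.96, gave 0.033 at half the information and 0.049 at full information.

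**3. What if either attempt could be claimed?** With two independent tests at 0.05, 1 − 0.95² = 0.0975. This is an upper illustration. It requires that the first data set remains usable as a result, and that the two attempts are independent.

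**4. What if the same centres are redrawn?** Under an independent 1:1 redraw, each new control centre has probability 0.5 of having been an intervention centre. With 40 centres and 20 per arm, the expected number of new controls already exposed to AI-HEALS is 20 × 0.5 = 10.

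**5. Rule and analysis basis side by side.** Statistical analysis promises intention to treat. Study management replaces the allocation and recollects data. The article does not say whether the same centres and participants are used again, or what becomes of the first allocation and its data. If the same people continue, they cannot be analysed both as first randomised and under the revised scheme.

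**The case against.** The best defence is that the stated trigger is staff adherence, not outcome results, and that a clean restart is valid. Step 1 bears this out. A reader might infer that the rule necessarily destroys the randomised comparison, or that no valid p-value could follow. The article does not support that, because harm needs a further step that the rule allows but does not prescribe.

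A reader might also infer that the research leaders see outcomes by arm as data accumulate. The article says only that blinding cannot be guaranteed. It gives the leaders supervision of procedures and, under Data Availability, access to the final data set. Interim sight of results by arm is possible but undocumented.

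A third tempting reading is that the first data are thrown away, in flat contradiction of intention to treat. The article does not say so, and intention to treat could be applied within a wholly new trial. That reading also cannot be combined with the 9.75% figure, which needs the first data set to remain available. Reuse of the same centres is likewise an assumption.

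The article calls the standards predefined, and a condensed article may leave them to the full protocol, so their absence here is not held against it. The clause is also contingent: if it is never triggered, the analysis is unaffected.

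What remains is that the sentence is a mandatory rule, the remedy does not fit the fault, and none of the conditions that would make a restart valid is imposed.

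**Conclusion.** The sentence is wrong as written and should be replaced. It orders a new allocation after data exist, for a reason unrelated to the allocation, without requiring a decision independent of results. It conflicts with analysis by the original allocation under intention to treat.

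The size of the harm depends on how the rule would be used:

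- **No inflation** (two-sided 0.05) for a result-independent restart in unexposed centres using only new data.
- **Favourable error of about 0.037-0.046 instead of 0.025** if the restart depends on interim results, under the assumed triggers z < 0 and z < 1.
- **At most 9.75% two-sided** if either of two independent attempts could be claimed.
- **About half of the new control centres already exposed** if the same centres are redrawn independently 1:1.

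No net direction of bias is established. Earlier exposure among controls could pull the contrast towards zero, whereas a restart after a disappointing start would favour the intervention.

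**What to change.** Replace the sentence in Study management with a rule to this effect:

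- The original allocation of community health centres is never revised.
- Failures to meet survey or follow-up standards are logged as protocol deviations, and the staff concerned are retrained.
- All data collected are kept.
- Every centre and participant is analysed as first randomised, with a sensitivity analysis that excludes the affected visits.

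The cost is a little extra deviation logging and one additional analysis. The article says that recruitment had not begun when it was written, so on its own account the change could be made before any centre was affected.

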### Population

The study population for our program is residents aged 18–75 years with T2DM in CHCs. The inclusion criteria are as follows: meet T2DM diagnostic criteria [65] (fasting plasma glucose ≥ 7.0 mmol/L or 2 h plasma glucose ≥ 11.1 mmol/L or HbA1c ≥ 6.5%); permanent residence in Beijing; ability to use smartphones and the WeChat chatting app; have not taken any psychotropic drugs prior to enrolment; have not participated in other studies; agree and able to adhere to the study. A history of type 1 diabetes, gestational diabetes, or secondary diabetes; severe diabetes complications; having radiotherapy or chemotherapy within the last six months; severe intellectual disability, Alzheimer's disease, or other mental disorders are key exclusion criteria. We have not yet started recruiting study participants, and we expect to begin recruitment in July 2023. After completing the entire questionnaire, participants will receive a gift of about 20 CNY. Participants will be informed that their participation is voluntary and that they can always opt out and switch to the SDPC.

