
All user data will be kept confidential. Participants have the option to withdraw from the study at any time. Adverse events related to the intervention will be recorded and reported in accordance with local procedures.

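### The safety rule requires the trial to be terminated after any adverse event in any participant, related or not, so it cannot sensibly be followed as written

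*Protocol article*

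**What the plan says.** The rule is in the protocol article, Methods, Study management, in the paragraph on the DMC and adverse events. The trigger is "If any participants experience AE or SAE, regardless of their relationship to the research intervention or whether the intervention has been implemented". The required action is that "the researchers must notify the investigators within 24 h of the event and terminate the trial".

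Four other statements bear on how to read it:

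- Earlier in Study management, for investigators who do not follow survey and follow-up standards: "research leaders will terminate the trial, revise the randomization scheme and recollect data after the modification is completed".
- In the DMC paragraph, if the committee finds protocol deviations or unauthorised changes: "they have the authority to suspend or terminate the study".
- At the end of the Intervention arm section: "Adverse events related to the intervention will be recorded and reported in accordance with local procedures". No stop is mentioned there.
- In Population, on a single person leaving: "they can always opt out and switch to the SDPC".

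Under Statistical analysis: "Variables analysis will be based on the premise of intention to treat". Under Outcomes, the primary outcome is the change in HbA1c, followed to 18 months.

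**The concern.** A stopping rule normally limits itself by seriousness, relatedness or a count, and has someone review the case first. This one expressly removes relatedness and start of intervention as limits. It covers non-serious as well as serious events, applies to any participant, and makes the action mandatory.

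The trial also expects events that would ordinarily be recorded as adverse events. Outcomes and Economic evaluation plan to collect hospital care and accident visits. The skills and self-efficacy scales ask about hypoglycaemia. Participants have type 2 diabetes, are aged up to 75 and are followed for 18 months.

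At stake is whether the primary outcome can be obtained at all or, on a milder reading, whether follow-up stays complete and unrelated to health events. There is a practical side effect too: staff who know that reporting a minor event stops the trial have a reason not to report it.

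**Working it through.** **Step 1. What terminating the trial means here.** The article supports three readings.

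- *Whole-trial stop.* This is the literal meaning. The two paragraphs of Study management use the trial to mean the whole study; revising the randomisation scheme ("research leaders will terminate the trial, revise the randomization scheme and recollect data after the modification is completed") makes sense only at that level. One person's exit is worded differently: opting out in Population, withdrawing in the Intervention arm section.
- *Pause and restart.* The same phrase in "research leaders will terminate the trial, revise the randomization scheme and recollect data after the modification is completed" is followed by resumed data collection, so a temporary stop is possible.
- *Exit of the affected person only.* This may have been intended, although the words do not say it.

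Nothing else in the article limits the rule. The sentence in the Intervention arm section covers related events only and is silent on stopping.

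**Step 2. How often the rule would be triggered.** There is no stated figure to reproduce. Inputs:

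- N = 320 (40 centres × 8) and 450 (45 × 10), from Study setting and randomization; N = 664, from Effect size.
- p = the chance that a participant has at least one adverse event over 18 months. This is an assumption, ranged from 0.1% to 5%, with events independent between participants.

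Chance that the rule is never triggered = (1 − p)^N:

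| p | N = 320 | N = 450 | N = 664 |
|---|---|---|---|
| 0.1% | 0.73 | 0.64 | 0.51 |
| 0.5% | 0.20 | 0.10 | 0.036 |
| 1% | 0.040 | 0.011 | 0.0013 |
| 5% | 7.4 × 10⁻⁸ | 9.5 × 10⁻¹¹ | 1.6 × 10⁻¹⁵ |

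Risk at which a trigger is as likely as not = 1 − 0.5^(1/N): 0.22% for N = 320, 0.15% for N = 450, 0.10% for N = 664.

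**Step 3. The milder readings.** The expected number of participants with an event is N × p, from N = 320 to N = 664:

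- p = 0.1%: 0.32 to 0.66
- p = 1%: 3.2 to 6.6
- p = 5%: 16 to 33

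If a pause was meant, each new event brings another stop. If a personal exit was meant, these are the people removed after randomisation.

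**Step 4. Comparison with the dropout allowance.** Effect size inflates 138 per cluster to 166. The loss that still leaves 138 is 1 − 138/166 = 28/166 = 16.9%. Exits at 5% are below that, so on the personal-exit reading adverse events alone would not exhaust the numbers, although ordinary dropout draws on the same allowance.

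**The case against.** The strongest reply is that a permanent stop is the least coherent reading. The article uses its words for stopping loosely, and in "research leaders will terminate the trial, revise the randomization scheme and recollect data after the modification is completed" termination is followed by resumption. Prompt reporting of adverse events to the Ethics Committee and regular DMC monitoring both presuppose a trial that continues after an event. On the personal-exit reading, nothing states that HbA1c measurement ends for that person. The expected exits fit within the dropout allowance, reasons for dropout are collected, and a mixed model under intention to treat is planned. The trigger probabilities rest on an assumed rate, and at 0.1% the trial more likely than not escapes the rule at all three sample sizes. What counts as a reportable event may be defined in a full protocol that is not shown.

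Part of this stands. The wording may well be loose drafting or translation. The probabilities describe how often the rule is triggered, and they measure loss of the trial only if the stop is permanent. That later HbA1c would be lost on the personal-exit reading is an inference, and no bias has been quantified.

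The defect remains. Staff and the Ethics Committee must apply the sentence as printed, and nothing in the article corrects it. A dropout allowance replaces numbers; it does not undo loss that depends on participants' health. A mandatory rule that is stated is not a detail left to a fuller document, and a definition of adverse events elsewhere would not cure the instruction to terminate.

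**Conclusion.** The rule is wrong as written and should be corrected before recruitment. Taken literally, it would very probably stop the trial before the 18-month HbA1c is complete: at a 1% event risk the chance of escaping it is 4% at best (N = 320) and 0.13% with 664 participants. Only a risk of about 0.1% to 0.2% or lower gives even odds of finishing. These figures assume independent events and a rate the article does not supply; the conclusion fails only if adverse events are extremely rare. On the pause reading the trial stops repeatedly. On the personal-exit reading the numbers are modest, about 3 to 7 people at 1% and 16 to 33 at 5%, but the exits follow health events after randomisation and work against the stated intention-to-treat principle. No conflict with the DMC clause is claimed.

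**What to change.** Delete the automatic termination and replace it with wording to this effect:

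> All adverse events and serious adverse events, related or not, are recorded and reported to the Ethics Committee in the same way in both arms, and the investigators are notified within 24 h. An affected participant may stop AI-HEALS if needed but stays in scheduled follow-up unless they withdraw. Suspension or termination of the whole trial is decided by the DMC or the Ethics Committee, for serious intervention-related safety concerns.

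Reword the adverse event sentence at the end of the Intervention arm section to match, since it now covers related events only.

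The cost is a change of protocol wording and an ethics notification. No patients, visits or procedures are added. The Population section says recruitment had not begun, so the change can be in place before the first participant is enrolled.
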